## Abstract

**Introduction:**

Poststroke hyperglycaemia is an independent risk factor for poorer outcomes in patients treated with mechanical thrombectomy (MT) and is associated with a lower probability of functional recovery and higher mortality at 3 months. This study aims to evaluate the association between glucose levels during cerebral reperfusion with MT and functional recovery at 3 months, measured by subcutaneous continuous glucose monitoring (CGM) devices.

**Methods:**

This prospective observational study aims to recruit 100 patients with ischaemic stroke and large anterior circulation vessel occlusion, in whom MT is indicated. CGM will be performed using a Freestyle Libre ProIQ device (FSL-CGM, Abbott Diabetes Care, Alameda, California, USA), which will be implanted on admission to the emergency department, to monitor glucose levels before, during and after reperfusion. The study’s primary endpoint will be the functional status at 3 months, as measured by the dichotomised modified Rankin Scale (0–2 indicating good recovery and 3–6 indicating dependency or death). We will analyse expression profiles of microRNA (miRNA) at the time of reperfusion and 24 hours later, as potential biomarkers of ischaemic-reperfusion injury. The most promising miRNAs include miR-100, miR-29b, miR-339, miR-15a and miR-424. All patients will undergo treatment according to current international recommendations and local protocols for the treatment of stroke, including intravenous thrombolysis if indicated.

**Ethics and dissemination:**

This study (protocol V.1.1, dated 29 October 2021, code 6017) has been approved by the Clinical Research Ethics Committee of La Paz University Hospital (Madrid, Spain) and has been registered in ClinicalTrials.gov (NCT 05871502). Study results will be disseminated through peer-reviewed publications in Open Access format and at conference presentations.

**Trial registration number:**

https://www.clinicaltrials.govNCT05871502.

STRENGTHS AND LIMITATIONS OF THIS STUDYThe GLIAS-mechanical thrombectomy (MT) is a prospective observational study that builds on previous research into the prognostic impact of hyperglycaemia in stroke patients treated with MT.Continuous glucose monitoring devices present a valuable opportunity to monitor glucose levels during MT and to investigate their impact at the time of reperfusion on the ischaemia-reperfusion damage.The observational nature of this study entails the possibility of biases.The fact that patients will be recruited in a single centre and the small sample size could be limitations for external validity.

## Introduction

 Poststroke hyperglycaemia is a very common complication in ischaemic stroke, affecting approximately two-thirds of patients, and is associated with poorer recanalisation rates, reduced perfusion, increased damage due to ischaemia-reperfusion and, consequently, poorer patient outcomes.^1 2^ Furthermore, hyperglycaemia can counteract the potential therapeutic effect of reperfusion treatments such as intravenous thrombolysis^3 4^ and mechanical thrombectomy (MT).^5^,^8^

Hyperglycaemia can cause damage through several pathophysiological mechanisms, including abnormalities in the blood–brain barrier and increased lactic acid production.^1 2^ Poststroke hyperglycaemia has been independently associated with poor outcomes after MT, with lower rates of functional recovery,^6 7 9^ a higher risk of haemorrhagic transformation^7 9 10^ and cerebral oedema^11 12^ and increased mortality at 3 months.^7^ The GLycemia in Acute Stroke (GLIAS) study was the first multicentre study to establish prognostic threshold for hyperglycaemia at 155 mg/dL, demonstrating a correlation between elevated glucose levels in the acute phase of stroke and poor outcomes, independently of stroke severity, infarct volume, diabetes or age.^13^

In patients treated with MT, the Solitaire Flow Restoration With the Intention for Thrombectomy (SWIFT) clinical trial showed that for each 10 mg/dL increase in blood glucose values, there was a 42% reduction in the probability of an excellent recovery at 3 months.^6^ It has yet to be determined whether administering insulin therapy prior to and during MT can mitigate the negative impact of hyperglycaemia in stroke recovery. Several studies have attempted to analyse this impact based on retrospective discrete determinations, such as glycaemia on admission^5 7 8 14^ and 24–48 hours after stroke,^15^,^17^ but none of them have monitored glycaemia during the MT procedure.

Despite the mounting evidence of its deleterious effects, poststroke hyperglycaemia is currently undertreated, which could be due to the lack of specific recommendations.^18^,^20^ The Highly Effective Reperfusion using Multiple Endovascular deviceS (HERMES) collaboration highlighted the significant variation in glycaemic management guidelines during the acute phase of stroke across various MT clinical trials: four of the trials had no specific recommendations, and one advised against hyperglycaemia treatment.^5^ Periprocedural management primarily focuses on blood pressure optimisation and selection of anaesthetic technique while glucose-level control is usually relegated to the postprocedural phase.^21 22^ In daily clinical practice, glucose levels are not monitored during the procedure, despite being one of the main modifiable prognostic factors in the acute phase of ischaemic stroke and closely related to reperfusion damage. Determining the impact of poststroke hyperglycaemia on patient outcomes could, therefore, lead to a paradigm shift in clinical practice.

The development and use of subcutaneous continuous glucose monitoring (CGM) devices^23 24^ provides an excellent opportunity to investigate the prognostic impact of poststroke hyperglycaemia in patients with acute stroke. CGM devices are minimally invasive, measure glucose levels in the interstitial fluid every 5 min and have been shown to be safe in patients with stroke during research studies,^25^,^29^ including those treated with intravenous thrombolysis^26^ and, more recently, in patients who underwent endovascular therapy.^30^ The feasibility, diagnostic accuracy and safety of CGM in the anaesthetic setting have also been demonstrated.^31^

Few studies have analysed the effect of hyperglycaemia after stroke on the levels of biomarkers of brain damage and repair.^32^ Recently, a number of micro-RNAs (miRNAs) have been proposed to modify the response to ischaemia-reperfusion injury and to regulate the expression of several elements essential for cell survival and apoptosis. Consequently, there is a growing interest in the potential role of miRNAs as biomarkers of ischaemia-reperfusion injury and even as potential therapeutic targets.

These miRNAs are of interest due to their functions, with previous studies demonstrating a role in cerebral ischaemia. In the context of ischaemic stroke, miR-339, miR-15a, miR-424 and miR-100 have been associated with large vessel occlusion.^33 34^ MiR-339, which is overexpressed in cases of cerebral and myocardial ischaemia,^35^ is related to neuronal survival and suppression of apoptosis in ischaemic conditions.^36^ MiR-15 and miR-424 have been linked to an antiangiogenic effect through VEGF inhibition.^37^ Additionally, miR-100 has been demonstrated to have an antiatherosclerotic effect.^38^ Furthermore, this miRNA exhibits varying levels in patients with cerebral infarction due to large vessel occlusion, suggesting a potential association with functional recovery.^33^ Finally, miR-29b has been demonstrated to attenuate ischaemic injury by negatively regulating the p53-dependent apoptosis pathway and could, therefore, be a potential target in diminishing cell injury in ischaemic stroke.^39^

We hypothesised that those patients with glycaemia values <155 mg/dL during MT and especially at the time of reperfusion will have less ischaemia-reperfusion injury, showing a different miRNA expression profile, with better neurological and functional outcomes and a lower risk of haemorrhagic transformation and cerebral oedema.

## Methods and analysis

### Design

#### Clinical study

Observational, unicentric, prospective study.

#### Patient population

The inclusion criteria are as follows: male and female patients older than 18 years, ischaemic stroke with anterior circulation large-vessel occlusion confirmed by imaging, indication of MT, previous modified Rankin Scale (mRS) 0–1, signed informed consent and enrolment prior to the MT procedure. Exclusion criteria are current drug or alcohol use dependence, imaging evidence of posterior circulation occlusion, comorbidity that prevents follow-up for 3 months after stroke or participation in another trial (table 1).

**Table 1 T1:** Inclusion and exclusion criteria

Inclusion criteria	Exclusion criteria
Male and female patients older than 18 years	Current drug or alcohol use dependence
mRS score before stroke of 0–1	Serious or life-threatening comorbidity that prevents follow-up for 3 months after the stroke
CT, angio-CT or angio-MRI evidence of stroke due to occlusion of a large vessel of the anterior circulation, including internal carotid artery (intracranial or extracranial) or middle cerebral artery (M1 or M2 segment) with indication for MT according to clinical practice	CT, angio-CT or angio-MRI evidence of posterior circulation occlusion
Informed consent signed and patient enrolment prior to the endovascular procedure	Participation in another therapeutic clinical trial

#### Randomisation

None (observational study).

#### Intervention

Patients who meet the inclusion criteria and none of the exclusion criteria will be invited to participate in this research study. The attending stroke neurologist will provide and explain the study information document to the patient (or to the patient’s family member if the patient is unable to give consent personally). This informed consent process will take place in parallel with the preparation of the MT and will not delay any therapeutic procedure. Whenever the informed consent has been signed by a family member and once the patient is able to consent, the patient will be informed about the research study and given the opportunity to reconsider or withdraw.

After signing the informed consent document and before starting the MT procedure, a subcutaneous CGM device will be placed, removing it on day 15 or at discharge, whichever comes first. CGM will be performed using a Freestyle Libre ProIQ device (FSL-CGM, Abbot Diabetes Care, Alameda, California, USA), which was selected from those currently available on the market, with previous studies documenting its safety and suitability for radiological procedures.

All patients will be managed according to current guidelines for the diagnosis and treatment of stroke, including the administration of thrombolytics if the established criteria for this treatment are met. Anaesthetic management, including the choice of general anaesthesia or conscious sedation, will follow the local protocols of the anaesthesiology department. Patients with glucose levels >155 mg/dL will receive insulin at the discretion of the attending physician, following the local protocols for managing hyperglycaemia in hospitalised patients and the guidelines for managing hyperglycaemia in patients with stroke (online supplemental table 1). Patients who underwent only angiography without MT treatment due to evidence of complete revascularisation at the time of arteriography will be excluded from the analysis.

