### Statistical analysis

Statistical analysis will be conducted with the assistance of the Clinical Trials Unit of La Paz University Hospital. To analyse the continuous variables, the following information will be collected: the number of participants, mean, SD, median, minimum, maximum and 25th and 75th percentiles. For the categorical variables, the frequency distribution and 95% CI will be provided.

Multivariate logistic regression analyses will be performed to evaluate the effect of glucose levels at the time of reperfusion on functional recovery at 3 months, adjusting for other factors that show statistically significant differences in the univariate analysis. Significance will be assessed using the likelihood ratio.

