## Discussion

This study represents a further step in the consolidated research into the prognostic impact of hyperglycaemia after stroke that began with the GLIAS study, the first prospective multicentre study to show that the glycaemic threshold associated with poor prognosis in acute stroke patients is 155 mg/dL.^13^ The GLIAS study also helped to highlight the significance of identifying and treating persistent hyperglycaemia.^40^ The GLIAS-II study (PS09/01781), funded by the Carlos III Health Institute (ISCIII), demonstrated the high incidence of non-response to conventional glycaemic control in patients with acute stroke and its association with poor outcomes.^18^ The GLIAS-III study (PI18/00991), currently finished and undergoing data analysis, is a multicentre, translational study analysing the impact of glycaemic variability evaluated by CGM on the progression of cerebral infarction in patients and in an animal model.^41^

The GLIAS-MT study aims to demonstrate that the impact of hyperglycaemia at the time of recanalisation is a critical modifiable prognostic factor, associated with greater brain damage, a different miRNA expression profile as a biomarker of damage, and poorer neurological and functional outcomes.

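### The Discussion aims to demonstrate a modifiable factor, but with insulin unassigned the study can show only a prognostic association, and the covariate rule could admit insulin given after reperfusion

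*Protocol article*

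**What the plan says.** All from the protocol article.

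- **Design and Randomisation:** a single-centre, prospective, observational study with no randomisation.
- **Abstract, Introduction:** the aim is to "evaluate the association between glucose levels during cerebral reperfusion with MT and functional recovery at 3 months".
- **Introduction, hypothesis:** "those patients with glycaemia values <155 mg/dL during MT and especially at the time of reperfusion will have less ischaemia-reperfusion injury".
- **Introduction, on insulin:** "It has yet to be determined whether administering insulin therapy prior to and during MT can mitigate the negative impact of hyperglycaemia". The same section remarks that glucose control is usually left until after the procedure.
- **Intervention:** "Patients with glucose levels >155 mg/dL will receive insulin at the discretion of the attending physician", following local protocols and stroke guidelines. The text does not confine this to the period after the procedure.
- **Data collection and management:** lists admission blood glucose, peak sensor glucose during thrombectomy, time above 155 mg/dL from arrival to recanalisation, details of insulin treatment including its timing, and the proportion given insulin in the first 24 hours after onset.
- **Statistical analysis:** multivariable logistic regression "to evaluate the effect of glucose levels at the time of reperfusion on functional recovery at 3 months", adjusted for other factors found significant in univariate analysis. It names neither a 155 mg/dL cut nor insulin.
- **Discussion:** the study "aims to demonstrate that the impact of hyperglycaemia at the time of recanalisation is a critical modifiable prognostic factor".

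**The concern.** To call a factor modifiable is to claim that changing it changes the outcome. That needs a comparison of patients whose glucose was brought down with similar patients whose glucose was not, and some reason to think the two sets are comparable. Here the treating doctor decides who gets insulin, and the stated analysis contains no such comparison. A positive result would show that high glucose at reperfusion marks a worse prognosis. Under the Discussion's aim it could be reported as evidence for a treatment target.

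The handling of insulin in the model matters for the same reason. Insulin given before reperfusion is part of how the reperfusion value arose. Insulin given afterwards is partly a response to that value. The stated covariate rule does not separate the two.

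**Working it through.** **1. The plan's own figure.** Sample size estimates gives alpha 0.05, power 0.80, control death-dependence 0.66, a difference of 30% and 15% loss. I read the 30% as points (0.66 v 0.36) and the test as two-sided.

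n = [1.96·√(2·p̄·(1−p̄)) + 0.842·√(p₁(1−p₁) + p₂(1−p₂))]² / (p₁−p₂)², with p̄ = 0.51

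- First term: 1.96 × √0.4998 = 1.386
- Second term: 0.842 × √(0.2244 + 0.2304) = 0.568
- n = (1.954)² / 0.09 ≈ 42.4, rounded up to 43 per group
- With 15% loss: 43/0.85 = 50.6, so 51; or 43 × 1.15 = 49.5, so 50

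The stated 50 per group reproduces. With 42.5 evaluable per group (50 × 0.85), power is 0.80. This point does not show the sample size to be wrong.

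**2. Aim against design.**

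| Section | What it supports |
|---|---|
| Abstract | association |
| Design; Randomisation | observational, nothing assigned |
| Intervention | insulin by clinical judgement |
| Introduction | effect of insulin before and during thrombectomy undetermined |
| Statistical analysis | outcome regressed on reperfusion glucose; no lowered-versus-high contrast |
| Discussion | demonstrate a modifiable factor |

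The first five rows agree with each other. The last claims more than they can deliver, and would do so even if no patient received insulin before reperfusion.

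**3. What a reperfusion value can mean.** Insulin may start above 155 mg/dL at any time after arrival. A patient at, say, 140 mg/dL at reperfusion may never have exceeded 155, may have exceeded it and been lowered by insulin, or may have fallen without insulin. This holds whether glucose is modelled as continuous or cut at 155. The article gives no frequency for these histories.

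**4. The covariate rule.** Any factor significant in univariate analysis enters. Insulin within 24 hours of onset is a recorded variable, and that window can include treatment given after reperfusion. High glucose at reperfusion makes such treatment more likely. If glucose is related to outcome, later insulin may well pass the screen for that reason alone. The model would then adjust for a consequence of the exposure, and the glucose coefficient would no longer describe the association the study sets out to estimate.

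**The case against.** **Loose Discussion wording.** The Abstract states the aim as association, and the strengths and limitations box admits possible bias from the observational design. This stands as a reason for moderate weight. It does not remove the point: the sentence is phrased as what the study aims to demonstrate, and the limitation as written does not mention insulin.

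**Already covered by the data, or by an unseen analysis plan.** The relevant variables are indeed collected, and prespecified strata may sit in a fuller document, so their absence from the article is not an error. The covariate rule is different. It is stated, and as stated it can admit post-reperfusion insulin.

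**No misclassification.** A patient below 155 at reperfusion is correctly classified on glucose at that moment, however the value arose. This stands. Earlier hyperglycaemia is a possible confounder, not an error in the exposure.

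**A stronger reading: a contaminated reference group and lost power.** A reader might assume that a share f of the <155 group was lowered by insulin and carries risk r, so that the group's risk is 0.36(1−f) + r·f. Against 0.66, with 42.5 per group:

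| f | r = 0.66: difference, power | r = 0.51: difference, power |
|---|---|---|
| 0 | 30 points, 0.80 | 30 points, 0.80 |
| 10% | 27, 0.71 | 28.5, 0.76 |
| 20% | 24, 0.61 | 27, 0.71 |
| 30% | 21, 0.50 | 25.5, 0.66 |

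The arithmetic is right, but the documents support no row over another. They give neither f nor r. Statistical analysis states no 155 cut, and Sample size estimates does not define its groups. The Introduction says glucose control usually follows the procedure, which points towards a small f.

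**A second stronger reading: the shared 155 mg/dL threshold is what defeats the claim.** It is not. The limit comes from insulin being unassigned, and would be the same with any treatment threshold.

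**Conclusion.** The point holds as a mismatch between aim and design, plus a covariate rule that needs a restriction. The study can establish that glucose at reperfusion is prognostic; it cannot establish that it is modifiable. That conclusion rests only on the stated design and needs no assumption about insulin use.

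That one reperfusion value can reflect different histories follows from the text, but its effect on the result has no known size and may be nil. The risk from post-reperfusion insulin is conditional: it arises if that variable is screened and proves significant. No power loss is claimed, and the sample size is not faulted. The change is worth making because it is cheap and because, once outcomes are known, any handling of insulin would be a post hoc choice.

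**What to change.** 1. **Discussion:** describe hyperglycaemia at recanalisation as a prognostic factor, matching the Abstract, and state that modifiability is not tested because insulin is not assigned.
2. **Statistical analysis:** bar insulin given after reperfusion from the covariates and report it descriptively only.
3. **Descriptive table:** report mRS 0–2 at 3 months by glucose history:
   - no reading above 155 mg/dL before or at reperfusion;
   - any reading above 155 before reperfusion but not at it, split by whether insulin was given before reperfusion;
   - above 155 at reperfusion.

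   Use admission blood glucose as well as the sensor record, since the sensor is placed only after consent.
4. **Sensitivity analysis:** add one version of the primary model that accounts for insulin given before reperfusion.

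Recruitment was ongoing at the time of the article and an intermediate analysis is planned after 50 patients, so these should be fixed before that look and posted to the registry as the article provides.

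**Cost:** wording, one table and one extra model, with no new data. The middle groups will be small and their intervals wide. If the sensitivity version excludes insulin-treated patients, it selectively removes hyperglycaemic patients and must be read that way. The study's claim becomes less ambitious. No change to the clinical insulin rule is implied.

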#### Study schedule

The study will last 3 months for each patient, according to the schedule illustrated in figure 1.

**Figure 1 F1:**
[figure not shown]
Study schedule. *Every patient fulfilling criteria for intravenous thrombolysis will be treated with it prior the performance of mechanical thrombectomy, per good clinical practice. **CGM devices will be removed at discharge or at day 15 in those patients still hospitalised. CGM, continuous glucose monitoring; mRS, modified Rankin Scale; NIHSS, National Institutes of Health Stroke Scale.

#### Primary endpoints

Stroke recovery at 3 months was measured by the dichotomised mRS (0–2 indicating good functional recovery and 3–6 indicating death or dependency).

#### Secondary endpoints

Infarct volume at 24 hours.The presence of any degree of haemorrhagic transformation and symptomatic haemorrhagic transformation at 24 hours.MicroRNA (miR-29b, miR-339, miR-15a, miR-100 and miR-424) expression profiles at the time of reperfusion and 24 hours later.Neurological recovery at 24 hours, using the National Institutes of Health Stroke Scale (NIHSS).Neurological and functional recovery at hospital discharge, using NIHSS and mRS.

#### Data collection and management

Glucose levels at the time of reperfusion in patients achieving thrombolysis in cerebral infarction (TICI) -2b, TICI-2c or TICI-3 recanalisation pattern after MT.mRS at 3 months. Its dichotomised assessment (mRS 0–2 indicating good functional recovery and 3–6 indicating death or dependency) is commonly used in acute stroke trials.Related to glycaemic control:Peak interstitial glucose levels during the MT procedure.Total time with interstitial glucose levels above 155 mg/dL from arrival in the emergency department to arterial recanalisation.Time with interstitial glucose levels in the range of 110–154 mg/dL: (a) from arrival at the emergency department to recanalisation; (b) during the first 24 hours and (c) during hospitalisation.Proportion of patients receiving insulin therapy for poststroke hyperglycaemia during the first 24 hours after onset of stroke symptoms.Insulin therapy received in clinical practice (time, route and dose).Number of CGMs with technical failures (missing or interrupted readings) or requiring replacement due to involuntary device removal or inadequate implantation.Additional CGM device data: mean interstitial glucose level, coefficient of variation.Related to MT:The number of MT passes (including aspiration and stent retriever passes).Degree of recanalisation according to TICI classification on final angiogram.Blood pressure in the emergency department and at the time of reperfusion.Related to stroke:Infarct size at 24 hours (assessed by a neuroradiologist who will be unaware of the glucose monitoring data).Haemorrhagic transformation at 24 hours (assessed by a neuroradiologist who will be unaware of the glucose monitoring data) is categorised into four types: (1) haemorrhagic infarction type 1 (HI-1)—small petechiae at the edges of the infarct area; (2) HI-2—confluent petechiae in the infarct area without mass effect; (3) parenchymal haematoma type 1 (HP-1)—haematoma occupying ≤30% of the infarct area with discrete mass effect and (4) parenchymal haematoma type 2 (HP-2)—haematoma occupying >30% of the infarct area with obvious mass effect.Symptomatic haemorrhagic transformation is defined as CT/MRI evidence of any type of haemorrhage associated with neurological deterioration ≥4 points on the NIHSS scale from baseline or leading to death.NIHSS score at 24 hours, at hospital discharge and at 3 months.Neurological or systemic complications during follow-up. The following complications will be systematically assessed at each visit: coma, seizures, early neurological deterioration, cerebral oedema, recurrent stroke, acute coronary syndrome, pulmonary thromboembolism, respiratory infection, urinary tract infection, sepsis and local haematoma or infection at the insertion site of the subcutaneous glucose monitor. Any other complication reported or detected during follow-up will be also recorded.Distribution of mRS scores at 90 days.Mortality at 3 months.Biomarkers of ischaemia-reperfusion injury: miR-29b, miR-339, miR-15a, miR-100 and miR-424. Samples will be drawn at the time of reperfusion and 24 hours later.Demographics: age, sex, race, weight, height, diabetes, hypertension, dyslipidaemia, coronary disease, atrial fibrillation, metabolic syndrome, chronic kidney disease with an estimated Glomerular Filtration Rate (eGFR)<60 mL/min/1.73 m^2^, smoking and alcohol abuse.Previous drug therapy: antiplatelets, anticoagulants, antihypertensives, antidiabetics and lipid-lowering agents.Stroke data: date of symptom onset (or last asymptomatic event in patients with unknown stroke onset), aetiological subtype of stroke and treatment with intravenous thrombolysis.Vital signs and laboratory values on admission at the emergency department: temperature, blood pressure, heart rate, respiratory rate, blood glucose and glycated haemoglobin.Treatment times: time from stroke onset to hospital admission; time from hospital admission to start of intravenous thrombolysis (door-to-needle time); time from hospital admission to start of MT (door-to-femoral puncture time); time from hospital admission to reperfusion; time from femoral puncture to reperfusion.Neuroimaging data: Baseline Alberta Stroke Programme Early CT Score, baseline collateral flow and baseline perfusion.

Blood samples for miRNA analysis will be drawn from the antecubital vein at the time of reperfusion and 24 hours later. The miRNA analysis will be performed in the Neurological Sciences and Cerebrovascular Research Laboratory of IdiPAZ. Total RNA enriched in miRNA will be isolated from patient blood samples using the RNeasy mini kit (Qiagen, Germantown, Maryland, USA). cDNA will be generated from the extracted miRNA and amplified by a real-time PCR performed using a LightCycler system (Roche Diagnostics), RNA probes (Qiagen) and specific primers for each selected miRNA.

